### Intervention

D(o)epression Blended [22] is an adaptation of the Dutch D(o)epression face-to-face program [24]. D(o)epression face-to-face is an individual CBT program based on the evidence-based treatment program Coping with Depression course for Adolescents [24]. All 15 sessions of the original D(o)epression face-to-face protocol were adapted for use in an online environment in four modules. Major adaptations included a shortening of the wording, more use of attractive visuals, and the possibility to interact online with the therapist. The online program can be combined with a minimum of 5 and maximum of 15 face-to-face sessions. The face-to-face sessions last 45 minutes each, and the adolescent and the therapist are present. Face-to-face sessions are scheduled when the adolescent starts with a new online module and at the end of the treatment, as is advised in the manual. More face-to-face sessions can be added when the therapist considers this helpful or necessary, with a maximum of 15. Additionally, there is unlimited contact between the adolescent and therapist through a chat function within the program. During the face-to-face contacts, online modules are introduced, the therapist invests in the therapeutic relationship, exercises are practiced, and suicide risk is examined. There are also two face-to-face contacts with the parents (when parents are involved): after 3 weeks and after the start of the fourth module. Parents receive psychoeducation, information about CBT, and suggestions on how parents can contribute to the treatment. All CBT therapists who will offer the D(o)epression Blended as treatment were trained by a registered clinical psychologist in how to provide blended treatment and in working with this specific blended treatment protocol in a 1-day training session.

The content of D(o)epression Blended is the same as that of the face-to-face intervention and consists of the following components: psychoeducation, setting realistic goals, self-monitoring, activation, improvement of social and communication skills, relaxation skills, cognitive restructuring, role play, problem-solving skills, and relapse prevention [25]. These components are divided into four online modules, which are offered sequentially and are called Start, Do, Think, and Future. The monitoring of mood and activities is completely online. The exercises are introduced during the face-to-face contacts and are practiced online and at home, which increases the generalizability to real-life situations. The therapist receives automatically generated prompts when the adolescent has completed a task and can view the content of the task. The online environment offers convenience, autonomy, and flexibility because adolescents can tailor their treatment preferences, such as pace, frequency, and location. This means that blended treatment is vastly different from regular treatment and allows for tailoring of the treatment to the preferences of each individual.

The control condition is TAU, which consists of a broad range of different treatments. Mental health institutions offer interpersonal therapy, family therapy, parent counseling, medication, mindfulness training, ACT (acceptance commitment therapy), psychodynamic therapy (short duration), (nondirective) counseling, creative therapy, and running therapy. For research purposes, CBT is not allowed within TAU.

### Study Outcome Measures

For an elaborate overview of study variables, see Table 1.

**Table 1 table1:** Overview of study variables.

Type of variable and concept		Instrument	Source			Assessment					
			Adolescent	Parent	Therapist	T0^a^	T1^b^	T2^c^	T3^d^	T4^e^	T5^f^
**Primary outcome**											
	Depression diagnosis	Kiddie Schedule for Affective Disorders and Schizophrenia	x	x		x			x	x	x
**Secondary outcomes**											
	Depression symptoms	Child Depression Inventory 2	x	x		x	x	x	x	x	x
	Depression severity	K-SADS	x	x		x			x	x	x
	Depression severity	Clinical Global Impression-Severity			x	x	x	x	x		
	Depression improvement	Clinical Global Impression-Improvement			x		x	x	x		
	Global functioning	Children Global Assessment Scale			x	x	x	x	x		
	Suicide risk taxation	Suicide Risk Taxation	x			x			x	x	x
	Comorbidity	Youth Self-Report scale/ Child Behavior Check List	x	x		x			x	x	x
**Cost-effectiveness**											
	Quality-adjusted life-years	EuroQol Questionnaire (EQ-5D-Y)	x	x		x	x	x	x	x	x
	Costs	Cost diary		x		x			x	x	x
**Moderators**											
	Gender, age, ethnicity, education, income	Demographic Characteristics	x	x		x					
	School or work	School Questionnaire	x			x			x	x	x
	Alcohol and drugs	Alcohol and Drugs	x			x			x	x	x
	Life events	Life Event Scale	x	x		x			x	x	x
	Degree of conflicts	Network of Relationships Inventory	x	x		x			x	x	x
	Parental depression	Beck Depression Inventory		x		x			x	x	x
	Parental psychopathology	Adult Self-Report		x		x			x	x	x
**Mediators**											
	Negative automatic thoughts	Cognitive Negative Cognitive Error Questionnaire	x			x	x	x	x		
	Cognitive emotion regulation	Cognitive Emotion Regulation Questionnaire	x			x	x	x	x		
	Attribution style	Children’s Attributional Style Questionnaire	x			x	x	x	x		
**Treatment characteristics**											
	Gender, age, experience, specialization of therapist	Therapy Procedure Checklist			x	x					
	Expectancy of treatment	Parent Expectancies for Therapy Scale	x	x		x					
	Previous treatments	Vragenlijst Eerdere Hulp en Interventies [History of Treatments]	x	x		x					
	Satisfaction treatment	Service Satisfaction Scale	x	x					x		
	Therapeutic alliance	Therapeutic Alliance Scale for Children	x		x		x	x	x		
	Cooperation with treatment	Cooperation With Treatment scale			x		x	x	x		
	Therapy questions	Therapy Questions			x		x	x	x		
	Treatment integrity	Observation			x				x		

^a^T0=baseline.

^b^T1=during the intervention after 5 weeks.

^c^T2=during the intervention after 10 weeks.

^d^T3=at 1 to 4 weeks postintervention.

^e^T4=at 6 months follow-up.

^f^T5=at 12 months follow-up.

### Primary Outcome Measure

Presence of the diagnosis of depression will be measured by the Present and Lifetime version of KSADS (K-SADS-PL) [26,27]. This widely used semistructured diagnostic interview assesses a wide range of diagnoses (present and lifetime), including their severity, taking into account the view of the adolescent and the parent, and will be conducted by a trained independent research assistant. Concurrent validity of the K-SADS-PL is supported; interrater agreement is high (93%-100%), and test-retest reliability is excellent for present and lifetime diagnoses of major depression [26].

#### Secondary Outcome Measures

Depressive symptoms will be measured with the Dutch version of the self-report measure Child Depression Inventory 2 [28,29], and with the Child Depression Inventory 2 parent version [28] rated by the parent. The severity of the depression will be assessed using the K-SADS-PL [26]. Severity of depression will also be assessed with the Clinical Global Impression-Severity scale [30], and improvement of depression will be assessed with the Clinical Global Impression-Improvement scale [30], both rated by the therapist.

Global functioning of the adolescent will be assessed with the therapist-rated Children Global Assessment Scale [31,32]. Suicide risk will be assessed with the K-SADS-PL [26], as well as with a self-report questionnaire Suicide Risk Taxation, which focuses on the frequency of suicidal thoughts, wishes, plans, and actions over the past 2 weeks. Comorbidity and psychopathology will be assessed with the K-SADS-PL [26], and additionally with the Youth Self-Report scale [33,34], rated by adolescents, and with the Child Behavior Check List for parents [33,34].

### Cost-Effectiveness Measures

Health-related quality of life will be measured with the Dutch version of the EuroQol Questionnaire (EQ-5D-Y) [35] and with the parent-rated EuroQol Questionnaire (EQ-5D proxy version) [35], which will be used to calculate quality-adjusted life-years.

The economic evaluation will be performed by registration of health care usage and costs in a cost questionnaire with a recall period of 3 months, which will be filled out by parents (which is identical to the one used in the previous RCT). Health care usage and registered costs that will be assessed are direct health care costs (eg, costs of psychologist, general practitioner, online treatment program, and medication), direct non-health care costs (eg, informal care), indirect costs (eg, monetary value of production losses caused by absence and reduced productivity and school), and out-of-pocket costs (eg, own contribution and transport costs). Costs will be calculated from a mental health care view and a societal view. The units of health care usage (eg, contact with the general practitioner, a session with a psychologist, costs of the online program) will be multiplied by the standard cost price obtained from the Dutch costing manual [36].

#### Moderators

Demographic information about the adolescents and parents will be assessed at baseline. Alcohol and drug use of the adolescents will be registered. Life events (such as bereavement, maltreatment, and suicide attempts), the date of occurrence, and their impact on the adolescent’s well-being will be registered with the Life Event Scale [37] by the adolescent and parent. The Network of Relationships Inventory will be filled in by both adolescents and parents to measure the degree of conflicts, such as quarrels, irritations, and antagonism, in the child-parent relationship [38]. Depressive symptoms in parents will be assessed with the Dutch version of the Beck Depression Inventory, second edition [39]. Parental psychopathology will be assessed with the Adult Self-Report [40].

#### Mediators

Negative cognitive errors will be measured with the Negative Cognitive Error Questionnaire [41], which consists of the subscales underestimation of the ability to cope, personalizing without mind reading, selective abstraction, overgeneralizing, and mind reading. Cognitive emotion regulation will be assessed with the Cognitive Emotion Regulation Questionnaire [42] consisting of several strategies as a response to experiencing stressful events, namely self-blame, other blame, rumination, catastrophizing, positive refocusing, planning, positive reappraisal, putting into perspective, and acceptance. Attributional style will be measured with the self-report Children’s Attributional Style Questionnaire [43], which contains three dimensions of attribution, namely internal-external, stable-unstable, and global-specific.

### Treatment Characteristics

At baseline, demographic information and information about education and experience of therapists will be assessed. Treatment expectancy will be measured with the Parent Expectancies for Therapy Scale [44], which will also be rated by adolescents in a revised version. Previous treatments for the adolescents’ depression, such as CBT, pharmacotherapy, self-help treatments, or alternative therapies, will also be reported by the adolescents and parents with the inventory of History of Treatments [45]. Adolescents’ and parents’ satisfaction with treatment will be assessed with the Service Satisfaction Scale [46]. Therapeutic alliance will be reported by the adolescent and therapist using the Therapeutic Alliance Scale for Children [47]. The degree of cooperation with treatment, as observed by the therapist, will be measured with the Cooperation With Treatment scale [48]. The content of treatment will be assessed with some questions on the procedure during the therapy, such as techniques used and amount of contact through email and chat. Treatment integrity will be checked by recording two randomly chosen sessions per patient that will be observed and rated by trained psychologists. Ratings will be based on the quality of the therapist (eg, empathy, motivating patient), content of treatment (eg, following protocol, attaining goals), and structure of the session (eg, setting agenda, following time schedule). Items will be rated on a scale from 0 to 3, in which 0=absent, 1=minimal, 2=largely, and 3=maximal. A mean score for treatment integrity will be calculated.

### Analyses

Intention-to-treat (imputed data) analyses and completer-only analyses will be conducted. Results will be reported in accordance with the CONSORT (Consolidated Standards of Reporting Trials) 2010 Statement [49].

#### Preliminary Analyses

Possible baseline differences in demographic and diagnostic characteristics between the three conditions—(1) D(o)epression Blended condition, (2) D(o)epression face-to-face condition, and (3) TAU condition (the latter two conditions from the RCT, which has already been conducted)—will be checked by means of ANOVA, MANOVA, and chi-square analyses. If these variables show differences between the conditions, they will be entered as covariates in all models and regression models to test the effectiveness of the intervention.

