**Methods:**

A pragmatic quasi-experimental controlled trial will be conducted to study the effectiveness of a blended CBT treatment protocol, in which blended CBT is compared with face-to-face CBT (n=44) and treatment as usual (n=44); the latter two were collected in a previous randomized controlled trial. The same inclusion and exclusion criteria will be used: adolescents aged between 12 and 21 years, with a clinical diagnosis of a depressive disorder, and referred to one of the participating mental health institutions. Assessments will be conducted at the same time points: before the start of the intervention, during the intervention (after 5 and 10 weeks), postintervention, and at 6- and 12-month follow-ups.

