#### Analysis of Primary Outcome

The primary outcome measure (ie, presence of depression diagnosis) is dichotomous and will be tested with logistic regression analyses comparing the percentage of depressive disorders in the D(o)epression Blended condition in this study to the percentage of depressive disorders in the D(o)epression face-to-face condition and the TAU condition from the previous RCT.

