### Recruitment

The trial began recruiting participants in November 2017, and end of study enrollment was March 2019. At this time, 42 children have been recruited.

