### Strengths and Limitations

One of the strengths of this study is that it is carried out in mental health institutions and that the targeted population of this study consists of adolescents referred for treatment of their depressive disorder. Participants were not recruited for treatment for the purpose of this study. This means that conclusions from the results of this research can be generalized to real-life mental health care. Additionally, the study will be conducted in several mental health care centers in the Netherlands. Therefore, our findings will not be based on the results of only one mental health institution, which adds to the generalizability of the results. Another strength is that we will compare a blended CBT treatment protocol to active treatment conditions: face-to-face CBT and TAU. Moreover, assessments will be based on multiple informants (ie, adolescents, parents, and therapists).

This innovative blended treatment has considerable potential. It incorporates the positive characteristics of online interventions, such as high accessibility, and the potential to be easily tailored to the daily lives of adolescents. To our knowledge, this is the first study on the effectiveness of blended CBT treatment of depressive disorders in adolescents. Therefore, we can uniquely contribute to the crucial evidence-based improvement of treatment protocols in mental health care.

A limitation is that the study is not designed as an RCT. In this study, we will recruit participants for the blended CBT condition only. The results of these participants will be compared with participants recruited in the earlier conducted RCT, in which face-to-face CBT was compared to TAU. Since there is no randomization in the current trial, it cannot be ruled out that there are slight differences in the participants, therapists, or societal context. We will try to keep this potential threat to internal validity as low as possible by working with the same inclusion and exclusion criteria for participants and with the same or similar mental health institutions. However, this pragmatic quasi-experimental design will deliver preliminary evidence and very relevant information on the effectiveness and cost-effectiveness of blended CBT in routine care.

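### Confounders enter this non-randomised comparison only if baseline tests show differences; at 42/44/44 that rule can leave measured confounding in the primary odds ratio

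*Protocol article*

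**What the plan says.** The abstract's Methods give the comparison and the size of the two historical arms: "blended CBT is compared with face-to-face CBT (n=44) and treatment as usual (n=44"). Under Results, Recruitment, enrolment has ended and the article reports "At this time, 42 children have been recruited". Sample Size had planned 70.

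Preliminary Analyses names what is screened: "Possible baseline differences in demographic and diagnostic characteristics between the three conditions". As for the method, the protocol says that these "will be checked by means of ANOVA, MANOVA, and chi-square analyses". The consequence follows: "If these variables show differences between the conditions, they will be entered as covariates in all models". No significance level is given for these checks.

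Under Analysis of Primary Outcome, the presence of a depression diagnosis "will be tested with logistic regression analyses comparing the percentage of depressive disorders" in the blended arm with those in the other two. No covariate is named there. Analysis of Secondary Outcomes, by contrast, always adjusts for the baseline level of the outcome analysed.

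Strengths and Limitations acknowledges the design problem. It concedes that "it cannot be ruled out that there are slight differences in the participants, therapists, or societal context", and gives the absence of random allocation as the reason. It relies on shared eligibility criteria and on the same or comparable centres to limit it.

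**The concern.** A baseline test asks whether two samples differ by more than chance. It does not ask whether a variable confounds the treatment comparison. In a randomised trial the distinction matters little, because imbalance is chance by construction. Here the blended patients are a later cohort and all eligible consenters receive blended CBT, so systematic differences are plausible. In arms of just over 40, a non-significant test is weak evidence of balance.

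Under the rule as written, a prognostic variable such as baseline severity stays out of the primary model unless a test happens to flag it, while an unrelated variable that is flagged goes in. At stake is the blended v TAU odds ratio, the main result: it may carry confounding from variables that were measured at T0 and could have been adjusted for.

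**Working it through.** **The plan's own figure.** The protocol gives no figure for how well its baseline checks detect imbalance. Its planned 70 concerns the treatment effect: 2 × (1.960 + 0.842)² / 0.53² = 55.9, so 56 per arm, and 56 / (1 − 0.20) = 70. That match says nothing about the covariate rule.

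**Inputs.** Arm sizes are 42 (Recruitment), 44 and 44 (abstract). Alpha for the baseline tests is not stated; two-sided 0.05 is assumed.

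**Step 1: continuous covariates.** Let the blended mean be shifted by d SD from both comparator arms. The noncentrality parameter of the three-group F test is

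λ = d² × n_B × (N − n_B) / N = d² × 42 × 88 / 130 = 28.43 d².

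Power is the probability that a noncentral F(2, 127, λ) exceeds the 5% critical value of 3.07.

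| True shift d | λ | Detected | Missed |
|---|---|---|---|
| 0.2 SD | 1.14 | 14% | 86% |
| 0.3 SD | 2.56 | 27% | 73% |
| 0.4 SD | 4.55 | 46% | 54% |
| 0.5 SD | 7.11 | 65% | 35% |
| 0.6 SD | 10.24 | 82% | 18% |

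Detection reaches 50% at about 0.42 SD and 80% at about 0.59 SD. With the planned 70 in the blended arm it would be 36% at 0.3 SD and 80% at 0.5 SD.

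**Step 2: binary covariates.** A three-group chi-square test at 42/44/44 detects 50% v 40% in 15% of trials, 50% v 35% in 29%, 50% v 30% in 50% and 50% v 25% in 72%.

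**Step 3: effect on the primary odds ratio.** This was simulated at 42/44/44 with no true treatment effect. Assumptions not taken from the documents: outcome rate about 40%, independent confounders each shifted 0.3 SD in the blended arm towards better prognosis, log-OR 0.5 per SD. A covariate enters the logistic model if its ANOVA p value is below 0.05.

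| Confounders | Median OR, plan's rule | Type I error, plan's rule |
|---|---|---|
| One | about 0.90 | about 5% |
| Two, same direction | about 0.86 | about 7% |
| Four, same direction | about 0.76 | about 9% |
| Four, mixed directions | about 0.99 | about 5% |

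Fixed adjustment for the same variables gives a median OR of about 1.0 and a type I error of 4% to 5%. Repeat simulations of the one-confounder case gave medians of 0.90 to 0.94 under the rule.

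The sign follows the assumed direction. With shifts towards worse prognosis of 0.3 to 0.5 SD, a covariate OR of 1.5 to 2.0 per SD for one confounder (1.5 for three) and a baseline rate of about 30%, the rule gives 1.06 to 1.08 with one confounder and 1.14 to 1.19 with three. Unadjusted values are 1.08 to 1.33 and 1.34 to 1.76. The rule therefore removes part of the confounding, but not all of it.

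**The case against.** The strongest reply is that the size of the harm rests on assumptions. The documents report no imbalance, no direction and no prognostic strength. With one confounder the type I error stays near 5%, and with mixed directions the bias cancels. The four-confounder, same-direction case is unfavourable by construction. This stands: the simulation shows what the rule permits, not what has happened.

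The plan also names MANOVA, which the ANOVA figures leave out. With four 0.25 to 0.3 SD shifts, a three-group MANOVA is significant in about 41% to 59% of trials. If that brought the whole tested set into the model, the OR would be 0.84 to 0.89 and the type I error 7% to 9%. The protocol does not say that it would. This softens the figures without removing the problem.

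Four stronger readings are tempting, and the documents do not support them:

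- A reader might infer that the rule misses most moderate imbalances. That holds below about 0.42 SD; at 0.5 SD it misses about 35%.
- A reader might infer that the primary effect is biased and its error rate wrong. Both are conditional on imbalances not yet known.
- A reader might take covariate adjustment as the only safeguard. Strengths and Limitations also relies on common eligibility criteria and comparable centres, Design on identical instruments, and the limitation is disclosed.
- A reader might expect adjustment to sharpen the odds ratio. In logistic regression it does not: with balanced arms and four prognostic covariates, the standard error of the log-OR rose from 0.44 to 0.50.

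The contrast with the secondary models also has limits. All participants have a depressive disorder at entry, so baseline diagnosis cannot serve as a covariate; severity is a different variable.

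Finally, the article states no threshold for showing differences, and an analysis plan not shown could replace the rule. The threshold is inferred from the named tests. The rule itself is written in the protocol.

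**Conclusion.** The point holds as a risk created by a stated rule. In a non-randomised comparison with arms of 42 to 44, making adjustment depend on baseline tests leaves about a third to three quarters of true 0.3 to 0.5 SD imbalances unflagged by a three-group ANOVA, and nothing else puts a covariate into the primary logistic model. The resulting distortion of the blended v TAU odds ratio is small with one modest confounder and material if several point the same way. The detection figures rest on the reported arm sizes, an assumed alpha of 0.05 and a shift of the blended arm against both comparators. The odds ratios rest additionally on assumed prognostic strength, number of confounders and outcome rate. The rule is better than no adjustment and worse than a fixed covariate set.

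**What to change.** Delete the test-based condition. State that the primary logistic model and all secondary models include a short, fixed set of T0 covariates whatever any test shows. One workable set is a single named baseline severity measure (such as the CDI-2 self-report score), age, gender and a single named comorbidity score. Name one instrument for each, so that no choice remains open. All are in the T0 schedule of Table 1, and Design says that the instruments match those of the earlier RCT, so no new data are needed.

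Limit the set to what the number of events supports. Four covariates plus two condition terms make six parameters; if there are 30 to 60 events among the 130 patients (an assumption), that is 5 to 10 events per parameter. At the lower end, use penalised or propensity-weighted estimation, and state that choice in advance.

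Show baseline balance as standardised differences rather than p values, and report the unadjusted model as a sensitivity analysis. Trial Status says that follow-up assessments were still under way, so the change should be made before the blended arm's 12-month outcomes are analysed.

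The cost is revised wording, a few degrees of freedom and a somewhat wider interval: 0.50 / 0.44 = 1.14, so about 14% wider on the log scale in the four-covariate simulation with balanced arms. Confounding by unmeasured factors or by calendar time remains and should stay among the stated limitations.
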